#### Primary outcome

Change in proportion of residents who are prescribed at least one PIM (from baseline to 12 months) according to the 2019 Beers Criteria [52]

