### Sample size

It was estimated that a conventional RCT with randomisation of individuals would be able to detect a reduction from 60 to 40% of residents having at least one PIM [14], with a minimum of 106 residents in each arm (total of 212 residents in both arms) with a significance level of 5%, a power of 80% on equal allocation and a response rate of 85%. By adjusting for the loss of power due to clustering, with an intra-cluster correlation coefficient of 0.05 and a cluster size of 93 residents per RACF, the estimated sample size is (1 + [(93–1) x 0.05] =5.6 x 106) or 594 residents in each arm (1188 in both arms), equating to a minimum of 13 sites. The sample size was calculated using G*Power 3.1.9.4 [57].

The estimated prevalence of PIM in RACFs at baseline (60%) was based on previous studies in which the prevalence of PIM in Australian RACF residents were reported as 73% in 2018 [16], 49% in 2014 [14] and 56% in 2012 [58].

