### Statistical analysis

Descriptive statistics will be used to summarise and compare the data at the RACF level in each group at baseline and at the end of the trial, including primary and secondary outcomes as well as additional potential confounder variables (such as demographic profile, duration of residency, presence of dementia, Charlson comorbidity index [59] and number of medical conditions).

Bivariate analyses for group comparisons will use either t tests or ANOVA for data that are normally distributed, Mann-Whitney U and Kruskall-Wallis tests for data that are not normally distributed, or chi-square-based analysis for categorical outcome data. For within group comparisons, paired t tests and repeated measures ANOVAs will be used; if variables are not normally distributed, the Wilcoxon signed-ranks and Freedman tests will be used, while the McNemar test will be used for changes in proportions.

To determine the effect of the intervention on the outcome measures and the changes over time (between-within group effects), multilevel modelling methods, which take into consideration the hierarchical structure of the data (including clustering within RACF and repeated measurement occasions) will be applied. These modelling methods will include mixed-effects generalised linear models (Logistic and Poisson regression models) for binary and count outcomes as well as mixed-effects linear models for continuous outcomes assumed to have a normal distribution, or otherwise transformed to meet the assumption.

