Analysis will be weighted by cluster size as required. Interactions and adjusting for demographic characteristics and other potential covariates will be included when deemed necessary. Residents who enter, die or move from RACFs after baseline data collection will have only one data point and will be included in the analysis. When data are missing at random, patterns of missing data will be evaluated, and potential predictors of missing responses will be investigated. Methodological attempts to fill in missing data will be extensively explored and applied as appropriate. These include single imputation approaches (such as regression imputation and nearest neighbours or hot-deck imputation) and multiple imputation approaches. Analysis will be conducted using either SPSS version 26 or STATA version 16. Significance level will be set at the usual 5% alpha-level (two-tailed where applicable). All estimated effects will be reported along with their 95% confidence intervals.

Since the sample size and power calculation have been devised based on the primary outcome and hypothesis, the level of adjustment and number of potential covariates to adjust for may be limited by the sample size and the response rate. Posterior power calculations will be performed based on available sample size and the secondary outcomes.

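### The missing-data rule puts single imputation on a par with multiple imputation and does not rule out imputing values after death

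*Protocol article*

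**What the plan says.** All the relevant sentences are in the Statistical analysis section of the protocol article.

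- On turnover: "Residents who enter, die or move from RACFs after baseline data collection will have only one data point and will be included in the analysis".
- On the missing-data mechanism: "When data are missing at random, patterns of missing data will be evaluated, and potential predictors of missing responses will be investigated".
- On filling in: "Methodological attempts to fill in missing data will be extensively explored and applied as appropriate".
- On the methods: "These include single imputation approaches (such as regression imputation and nearest neighbours or hot-deck imputation) and multiple imputation approaches".

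The same section plans mixed-effects models that allow for the hierarchy in the data, "including clustering within RACF and repeated measurement occasions". Table 2 shows that medication lists are taken only at baseline and at 12 months. A resident who dies in between therefore has one list and no second one.

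**The concern.** A protocol may leave missing-data detail to the analysis plan. This one goes further and endorses a class of methods. In the three forms of single imputation it names, each gap receives one value, and an ordinary analysis then counts that value as data. Neither the uncertainty about the filled value nor the loss of real observations reaches the standard error. Nothing limits these methods to secondary outcomes or covariates, so they are open for the primary outcome.

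The scope is also unclear. The turnover sentence and the imputation sentences are not tied together, and death is not separated from a chart that could not be retrieved. A 12-month prescription after death does not exist, so there is nothing to recover. The planned within-group paired tests (McNemar, paired t, signed-ranks) cannot use a resident with a single observation. An analyst could read the promise to include such residents as a reason to fill in the other value.

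At stake are the width of the confidence interval and the false-positive rate for the primary comparison.

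**Working it through.** **Inputs.** The Sample size section gives 93 residents per facility, an intra-cluster correlation of 0.05 and 594 residents per arm. The last figure reproduces: 1 + 92 × 0.05 = 5.6; 106 × 5.6 = 593.6, or 594; 1188 / 93 = 12.8, or 13 sites. Alpha is 5%, taken as two-sided. The share of values filled in, f, is not in the document. I assume 15%, 30% and 40%. The 15% has the same size as the shortfall implied by the stated 85% response rate, but it is not a documented rate of death or departure. The plan states no standard error or error rate under imputation, so there is no figure of its own to reproduce here.

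**Without clustering.** Take n residents per arm, a share f filled by random draws from the observed residents of the same arm, and outcome variance pq.

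- Reported variance of the arm proportion: pq/n.
- True variance: pq/[n(1−f)] from having fewer real observations, plus f·pq/n from the random draws.
- Reported SE / true SE = √{(1−f) / [1 + f(1−f)]}.
- f = 0.15: √(0.85/1.1275) = 0.87; type I error ≈ 2Φ(−1.96 × 0.868) = 8.9%.
- f = 0.30: √(0.70/1.21) = 0.76; type I error ≈ 2Φ(−1.96 × 0.761) = 13.6%.

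**With clustering, arm-wide donors.** Filling from the whole arm pulls each facility mean towards the arm mean, so the facilities look more alike than they are. Variances below are in units of pq.

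- f = 0.15 (79 of 93 observed, 14 filled): variance of an observed facility mean 0.05 + 0.95/79 = 0.0620; donor noise 14/93² = 0.0016. Apparent variance (79/93)² × 0.0620 + 0.0016 = 0.0464; true variance 0.0620 + 0.0016 = 0.0636. SE ratio √(0.0464/0.0636) = 0.85.
- f = 0.30 (65 observed, 28 filled): 0.05 + 0.95/65 = 0.0646; noise 28/93² = 0.0032. Apparent (65/93)² × 0.0646 + 0.0032 = 0.0348; true 0.0678. SE ratio 0.72.

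**Simulation.** No true effect, values missing completely at random, prevalence 50%. There were 20,000 runs at 594 per arm without clustering. There were 4,000 runs with 14 facilities of 93 (seven per arm, so that arms are equal), ICC 0.05 and a t test on facility proportions. Cells give SE ratio and type I error.

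| Setting | f = 15% | f = 30% | f = 40% |
|---|---|---|---|
| No clustering, donors from the arm | 0.87; 9.0% | 0.76; 14.0% | 0.70; 17.4% |
| Clustered, donors from the arm | 0.84; 9.1% | 0.71; 14.8% | 0.62; 20.3% |
| Clustered, donors from the same facility | 0.99; 5.0% | 0.99; 5.5% | 1.00; 4.9% |
| Clustered, nothing imputed | 1.00; 4.8% | 0.99; 5.1% | 1.02; 4.7% |

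Formula and simulation agree within simulation error. The facility-level t test stands in for the planned logistic mixed model, which was not simulated.

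**The case against.** The strongest reply is that the plan does not intend to impute for residents who died or left. A reader might infer from the imputation sentences that it would, but the document does not support that. It deals with these residents first and separately, and says they have one data point and are included. That reads most naturally as analysing the single observation in the mixed model. What stands against the plan is only that imputation after death is not excluded. Nor should everyone who leaves be grouped with the dead: a resident who moves still has prescriptions, although not in the trial facility.

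The imputation sentences also have other plausible targets: chart-based covariates such as dementia and comorbidity, or records not reached because of COVID-19 access limits, which the Data collection section anticipates. This stands. That most gaps come from turnover would be inference.

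A reader might also conclude that standard errors will be too small. That is too strong. Multiple imputation is listed as well, the mixed model needs no imputation, and same-facility donors kept type I error near 5%. A bias towards no effect would need donors drawn without regard to arm. With donors that ignore both arm and facility, a 20-point difference would become 20 × 0.85 = 17 or 20 × 0.70 = 14 points. Nothing in the text suggests such a procedure.

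Finally, the open wording might suggest that the method will be picked after the results are seen. An analysis plan that is not shown may fix the choice, so this is not held against the protocol. That does not rescue the listing itself, which is a stated choice.

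**Conclusion.** The point holds in a limited form. The protocol accepts single imputation as an equal of multiple imputation for any outcome, and it does not separate non-existence after death from a missing record. For random hot-deck with arm-wide donors and an assumed 15% to 30% filled in, the reported standard error falls to about 0.87 to 0.76 of its true value, or 0.84 to 0.71 with clustering, and type I error rises to about 9% to 15%. These figures rest on assumed shares, on data missing completely at random, and on a donor pool that the plan leaves open. They show what the wording permits and do not forecast what will happen. The remedy is cheap because the main analysis it needs is already planned.

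**What to change.** Change the missing-data paragraph as follows.

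1. Delete single imputation from the list of methods.
2. State that the mixed model on all observed occasions is the primary analysis, with residents who enter, die or move contributing their one observed point.
3. State that 12-month values are not imputed after death, and that no value is imputed for an occasion when the resident was not living in the facility.
4. For charts truly missing for residents present at a visit, use multiple imputation that respects facility clustering and includes arm and time, as a sensitivity analysis.

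The cost is a few sentences and slightly wider confidence intervals, with no new data collection. The mixed model still treats the unobserved occasions as missing at random given what it contains. The change removes the false precision but does not test that assumption.

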### Economic evaluation

A within trial cost consequence followed by a cost-effectiveness analysis will be conducted. The cost consequence analysis will explore the incremental impact (compared to the control arm) of the intervention on the disparate secondary outcomes, providing more information to decision makers in addition to a having a focus on the primary outcome. For the cost-effectiveness analysis, effectiveness will be measured in terms of the primary outcome—avoided PIM (reduction of the number of residents who take at least one PIM). A public health sector perspective will be used. All resource use will be valued in 2020/21 Australian dollars without discounting. Total costs for the intervention and control groups will be calculated, as well as average costs per participant, incorporating any additional costs relating to the delivery of the intervention (e.g. additional training, time that a GP spends on reviewing pharmacist recommendations). Resource use captured during the trial will include health service utilisation by each participant (ED visits, hospital admissions, ambulance transfer during the 12 months of control/intervention period; and medications used at baseline and at 12 months). Analogous multilevel modelling described above (controlling for differences in characteristics of participants and RACF clusters) will be used to estimate average cost per participant for both intervention and control groups. An incremental cost-effectiveness ratio (ICER) will be computed by comparing the costs and outcomes of the intervention and control groups. Results will be expressed as incremental cost per incremental reduction in the proportion of residents taking at least one PIM. Mean estimates will be used, and confidence values and sensitivity analysis will indicate the robustness and validity of the results and test any assumptions used. Uncertainty around the ICER will be explored using cost-effectiveness acceptability curves.

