## Background

Older adults residing in residential aged care facilities (RACFs) generally have complex co-morbidities and are prescribed a large number of different medications [1]. Studies have reported that, on average, RACF residents take between 9 and 11 regular medications [2–4]. Polypharmacy increases the risk of medication-related problems and adverse drug events, including hospitalisations, placing a significant burden on residents and economic cost on the health care system [5–7]. Australian studies have shown that almost all RACF residents have at least one medication-related problem [4, 8–11] and between 30% and 73% of residents are prescribed at least one potentially inappropriate medication (PIM) [4, 12–18]. According to a recent meta-analysis of 33 international studies, the use of PIM is significantly associated with an increased risk of hospitalisation in the older population, and the risk was higher in those who took more than one PIM [19]. Additionally, PIMs are associated with other potential adverse outcomes in older indivisuals, including fall, fracture, cognitive decline, delirium, stroke and cardiovascular events [20, 21].

Among PIMs, sedatives, antipsychotics and drugs with anticholinergic properties are particularly associated with greater risk of harm. A large Australian cohort study among 11,368 residents found that 61% were taking psychotropic medications, with the majority of these agents having sedative properties that can contribute to falls or confusion [22]. The over-use of psychotropic medications has been recently highlighted in the interim report of the Australian Royal Commission into Aged Care Quality and Safety [23]. Australian studies have reported that over 20% of RACF residents were taking antipsychotics regularly [22, 24], and the duration of antipsychotic use was longer than recommended [25–27]. Prolonged use of antipsychotics in older people is linked with increased risk of hospitalisation, hip fracture, peneumonia, stroke and death [28, 29]. Another large Australian study [30] of 17,000 RACF residents reported that 46% were taking drugs with moderate to strong anticholinergic effects; these drugs can contribute to cognitive and functional decline, delirium, worsening dementia, and increased mortality in older people [31].

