#### Secondary outcomes

Rate of unplanned ED presentations and hospital admissions per resident collected from RACF records over 12 monthsPolypharmacy—number of regular medicationsChange in proportion of residents who are prescribed at least one psychotropic medicine (defined as antipsychotics and benzodiazepines), excluding those residents with major psychiatric diseases or epilepsy (from baseline to 12 months)Change in dose of psychotropic medicines (measured as chlorpromazine or diazepam equivalent daily dose [55] (from baseline to 12 months)Change in residents’ Anticholinergic Cognitive Burden Score (ACB) [56] (from baseline to 12 months)Rate of staff influenza vaccination measured at the end of influenza season, from RACF recordsFall rate per resident, as documented from RACF fall records over 12 monthsChange in time spent on medication administration rounds per RACF, through observing randomly selected medication rounds [47] (from baseline to 12 months)Change in appropriateness of medicine dose form modification per RACF, through observing randomly selected medication rounds [47] (from baseline to 12 months)Change in proportion of residents who have drug allergies or adverse drug reactions documented in their RACF records (from baseline to 12 months)Number of medication-related incidents over 12 monthsCost-consequence and cost-effectiveness of the intervention over 12 months

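### The rule to transform non-normal outcomes carries over to costs, where it conflicts with the arithmetic mean cost that the ICER needs

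*Protocol article*

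**What the plan says.** The Economic evaluation section borrows its cost model from the main analysis: "Analogous multilevel modelling described above (controlling for differences in characteristics of participants and RACF clusters) will be used to estimate average cost per participant". It also states that "Mean estimates will be used, and confidence values and sensitivity analysis will indicate the robustness and validity of the results", and that "Results will be expressed as incremental cost per incremental reduction in the proportion of residents taking at least one PIM".

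The models it points to are in the Statistical analysis section. Binary and count outcomes get "mixed-effects generalised linear models (Logistic and Poisson regression models) for binary and count outcomes". Continuous outcomes get "mixed-effects linear models for continuous outcomes assumed to have a normal distribution, or otherwise transformed to meet the assumption". The transformation is conditional on non-normality. Neither the transformation nor a way back to the original scale is named, and no separate model is given for costs.

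The primary outcome is on the proportion scale: "Change in proportion of residents who are prescribed at least one PIM (from baseline to 12 months". One secondary outcome falls under the same rule for continuous data: "Change in dose of psychotropic medicines (measured as chlorpromazine or diazepam equivalent daily dose". Its definition does not say whether residents who take none of these medicines are included.

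**The concern.** The resources to be costed include ED visits, hospital admissions, ambulance transfers and medicines. A few residents with long stays will usually dominate such totals, so right skew is to be expected. The imported rule then calls for a transformation. A decision maker needs the difference in arithmetic mean cost, because only the arithmetic mean multiplied by the number of residents gives the total bill. A transformed-scale mean taken straight back to dollars is a different quantity (a geometric mean if the transformation is a log), and its gap from the arithmetic mean depends on the spread in each arm.

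The intervention may well change that spread, for example by preventing some long admissions. The error then need not cancel between arms. Cost-effectiveness is one of the four stated objectives and the results are meant for policymakers, so the numerator of the ICER should not depend on how one sentence in another section is read.

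A related question arises for equivalent dose. If all residents are analysed, many values will be exactly zero, and the same rule is then the only one offered.

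**Working it through.** **Figures in the protocol.** There is no cost level, cost spread or ICER to reproduce. The cost figures below rest on assumed values and are shown as a range.

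**1. Size of the gap for mean cost.** For lognormal cost with coefficient of variation CV, the ratio of geometric to arithmetic mean is 1/√(1 + CV²).

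| CV (assumed) | Ratio |
|---|---|
| 1 | 1/√2 = 0.71 |
| 1.5 | 1/√3.25 = 0.55 |
| 2 | 1/√5 = 0.45 |
| 3 | 1/√10 = 0.32 |

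**2. Effect on the difference between arms** (assumed means and CVs).

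- Equal spread: control 10,000 and intervention 11,000, both CV 2. The arithmetic difference is +1,000. The geometric difference is 0.447 × 1,000 = +447. The sign is right and the size is not.
- Unequal spread: control 10,000 with CV 2, intervention 9,000 with CV 1.5. The arithmetic difference is −1,000. The geometric means are 10,000/√5 = 4,472 and 9,000/√3.25 = 4,992, a difference of +520. A saving appears as an extra cost.
- The reverse: control 10,000 with CV 1.5, intervention 11,000 with CV 2. The arithmetic difference is +1,000. The geometric means are 5,547 and 4,919, a difference of −628.

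An untransformed model, or a suitable retransformation, removes the gap.

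**3. The ICER denominator.** Inputs from the Sample size section: 60% falling to 40%, ICC 0.05. Taking 0.05 as the ICC on the logit scale (an assumption), the random-intercept variance is 0.05/0.95 × π²/3 = 0.173, an SD of 0.416. Solving the logistic-normal integral for marginal proportions of 0.60 and 0.40 gives a conditional odds ratio of 0.430, against a marginal one of (0.4/0.6)/(0.6/0.4) = 0.444.

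- Averaging the model's predicted probabilities over the random effect returns 20.0 points.
- Applying the conditional odds ratio directly to a 60% baseline gives odds of 1.5 × 0.430 = 0.645, a proportion of 0.392, and so 20.8 points.
- If the repeated measurements are handled by a resident-level random effect with an assumed SD of 1, 2 or 3, that shortcut gives 24.0, 31.7 or 39.5 points. Averaging still returns 20.0.

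The mixed logistic model can therefore supply the denominator, provided that predicted proportions and not the raw odds ratio are used.

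**4. Equivalent dose.** The Background cites that "over 20% of RACF residents were taking antipsychotics regularly", so up to about 80% of residents would have zero antipsychotic dose if everyone is analysed. In simulated doses with 80% zeros and lognormal doses among users, log(1 + x) and the square root both leave 80% of values at the minimum, with skewness 1.7 and 2.8. No monotone transformation spreads out a point mass. The outcome is a change in dose, which adds negative values that a plain log cannot take.

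**The case against.** The strongest reply is that the protocol never says costs will be transformed. The models are called analogous, not identical; the transformation is conditional and no log is named; the stated purpose is average cost per participant; and mean estimates are promised. An untransformed linear mixed model is also within the rules and gives arithmetic means. All of this stands. A reader might infer that the stated models necessarily yield geometric-type means, and the text does not support that. What remains is that the only instruction for non-normal continuous data is to transform, that costs are the variable most likely to trigger it, and that the protocol does not say which instruction yields.

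A reader might also infer that the primary effect, and with it the denominator, will be an odds ratio on the wrong scale. The documents do not support this. The Primary outcome and Economic evaluation sections both fix the proportion scale, and the same mixed logistic model delivers it. The larger discrepancies in step 3 rest on resident-level SDs that appear nowhere in the protocol and arise only if the odds ratio is read naively. The prediction step is detail that an article may leave to the analysis plan.

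Two further points are not faults here. Scaling cost to length of stay is analysis-plan detail, and admission and discharge dates are collected. The dose point is conditional: the outcome definition does not settle whether non-users enter, and the 80% is an upper bound from background literature, for antipsychotics only.

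**Conclusion.** The concern holds for costs. A stated rule, carried into the Economic evaluation section by reference, misfires for skewed costs and conflicts with that section's own reliance on means. If a log is used and naively reversed, mean cost would be reported at 0.71 to 0.32 of its true value for CVs of 1 to 3, and the cost difference can change sign when the arms differ in spread. These sizes assume lognormal costs, a log transformation and no proper retransformation; none of these is stated in the protocol. They show what the rule permits, not what will happen.

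For the denominator, the point is only to name the scale in the same sentence. For equivalent dose, the rule fails if non-users are included and otherwise may not. Sample size is unaffected.

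**What to change.** In the Economic evaluation section, state that the transformation rule does not apply to costs and that arithmetic mean cost will be modelled untransformed. Either use a linear mixed model, or a gamma mixed model with log link from which arithmetic means are predicted for each arm. A gamma model needs positive values, so say how any resident with zero total cost is handled.

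In the same place, state that the ICER denominator is the standardised (marginal) difference in proportions from the mixed logistic model, with its confidence interval.

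For equivalent dose, state whether non-users are included. If they are, exempt this outcome from transformation too, and use an untransformed mean difference or a two-part model.

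Intervals should suit the planned minimum of 13 facilities, about 6 or 7 per arm, for instance with a small-sample degrees-of-freedom correction. A plain bootstrap that resamples facilities is doubtful with so few, and the uncertainty behind the acceptability curve should not rest on it alone.

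The cost is a few sentences and a little more analysis code. No new data are needed.
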